### 2.6. Governance and Ethics

Ethical approval for the study was obtained from the Medical Research Ethics Committee (MREC) of Ministry of Health, Malaysia (NMRR-19-3482-50546) and Research Committee of Universiti Putra Malaysia (JKEUPM) (JKEUPM-2019-464).

The research team comprises a multidisciplinary team, which includes the principal investigator (PI), an endocrinologist, a dietitian, a biochemist, and a Ph.D. student. The PI will develop the study protocol, verify progress reports to the funder, oversee the study progress, and ensure the scientific accuracy of study results. The endocrinologist will oversee the OGTT process and stratify subjects into NGT, prediabetes, or T2D groups based on the OGTT and HbA1c results. The dietitian will administer the food frequency questionnaire (FFQ) and the 3-day dietary recalls; take anthropometric measurements; and calculate the energy and nutrient intakes of the subjects. The biochemist will be responsible for offsetting up and storing metabolomic reagents and buffers; plasma and urine sample storage; liaising with the metabolomic science officer regarding ^1^H NMR sample run; preprocessing spectral data on Chenomx NMR suite software; metabolite profiling; and metabolomic pathway identification. Finally, the Ph.D. student will be responsible for the day-to-day management of the study; procurement of equipment and chemicals; training of enumerators; subject recruitment and enrolment at the study sites; liaising with commercial laboratory regarding blood tests; and centrifugation of plasma and urinary samples for metabolomic analysis. The Ph.D. student will also be responsible for communicating with the medical doctors, nurses, phlebotomists, and medical assistants at the study sites to ensure the subjects’ safety and care. Additionally, the Ph.D. student will manage the overall administrative, technical, logistic, and fiscal responsibilities; communicate with all members of the research team; and will be responsible for the ethics application and renewal. The entire research team will work together on multivariate data analysis of processed spectra on SIMCA-P+ software, identifying nutritype signatures and determining their association with T2D.

### 2.7. Statistical Analysis

Statistical analysis will be performed using SPSS statistical software version 25.0 (IBM, Chicago, IL, USA). Data for categorical variables will be reported as number and percentage, while continuous data will be reported as mean ± standard deviation (SD). Data normality will be assessed prior to data analysis. The study will analyse the differences in the demographic characteristics between subjects who agreed to participate in the study versus those who did not agree to participate. Pearson’s correlation coefficient test will be used to determine correlations between continuous variables, the Chi-squared test to determine the association between categorical variables, and one-way analysis of variance (ANOVA) to compare the differences between the three groups. Multivariate linear regressions will determine the association between the metabolomic profile and factor scores of each dietary pattern yielded from PCA. Multinomial logistic regression will determine the factors, and the nutritype signature models associated with T2D. Variables significant at the bivariate level will be entered into the regression model as confounders. Crude and adjusted odds ratios (ORs) with a 95% confidence interval (CI) will be presented. Subgroup analyses will also be performed, such as early versus late postpartum (<1 year versus ≥1 year post-GDM), supplement versus nonsupplement users, and obese versus nonobese subjects. A previous study found different risk factors of T2D at early (<1 year) versus late postpartum (≥1 year) following GDM [4]. In case of missing data, the study will report the number of available data for the variable. We will analyse any differences in the characteristics between reporters versus nonreporters. A *p*-value < 0.05 for all statistical tests will be considered significant.

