### 2.1. Design

This is a comparative cross-sectional study involving women post-GDM, named the Malaysian Nutritype (MyNutritype) study. The primary outcome is the nutritype signatures associated with T2D in Malaysian women post-GDM. The secondary outcomes of the study include the comparisons of anthropometric and clinical measurements, biochemical profile, energy and nutrient intake, and lifestyle practices between the three groups of women post-GDM (NGT, prediabetes, and T2D).

The aims of this study are:(a)To determine dietary patterns associated with T2D and prediabetes;(b)To determine the metabolomic profile associated with T2D and prediabetes using one-dimensional proton nuclear magnetic resonance (^1^H NMR) spectroscopy;(c)To identify nutritype signatures (association between dietary patterns and metabolomic profile);(d)To determine the nutritype signatures associated with T2D in women post-GDM;(e)To compare other parameters in women post-GDM with normal glucose tolerance (NGT), pre-diabetes and T2D, which include:i.Anthropometric and clinical measurements;ii.Biochemical profile;iii.Energy and nutrient intake;iv.Lifestyle practices.

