### 2.3. Study Population

The study will include Malaysian women aged 18–49 years with a previous diagnosis of GDM. Exclusion criteria will be the following: pregnant women, recent hospitalisation within the last 6 weeks, and previously diagnosed medical problems (such as type 1 or type 2 diabetes, cancer, and liver or renal disorders). The sample size will be estimated using the mean difference formula [20]. Based on a study that compared dietary intake and metabolomic profile in NGT, prediabetes and metabolomic profile in women post-GDM in Gothenburg, Sweden [14], considering a 95% confidence level and 80% power, a total of 99 subjects will be needed for the study. To account for nonresponse or refusal to participate, an additional 20% of subjects will be required, leading to a minimum of 126 subjects.

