#### 2.5.2. Sociodemographic Characteristics and Obstetric History

The study will collect sociodemographic data on age, ethnicity, education level, marital status, occupation, household income, and household size using a structured questionnaire. A family history of diabetes will also be assessed. Information on obstetric history will be obtained from the antenatal records. This will include gravidity, parity, pre-pregnancy weight, gestational weight gain, postpartum weight retention, number and timing of GDM diagnosis, duration lapse since GDM diagnosis, treatment during GDM, delivery method, birth outcomes, infant birth weight, breastfeeding duration, and family planning.

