## 3. Discussion

The study aims to identify the nutritype signatures associated with T2D in women post-GDM using the ^1^H-NMR-based metabolomics approach. Cross-sectional studies in Malaysia found the that the prevalence of T2D in women post-GDM ranges between 0.8% and 6 weeks to 35.5% at 15 years postpartum [44,45,46]. This indicates that regardless of the year of diagnosis, having a previous diagnosis of GDM significantly increases future T2D risk.

Metabolomics has emerged as a crucial tool in discovering dietary biomarkers. Alterations in the metabolome are also implicated in disease development, as they respond to nutrients, disease and stress [19]. Traditional methods for assessing dietary intake, including FFQ, may be prone to bias, recall errors, and underreporting [47]. Dietary biomarkers, on the other hand, provide a more objective and accurate measure of food intake [47]. Together, the use of traditional dietary assessment and metabolomic profiles can improve the accuracy of dietary assessment [47].

In the Malaysian context, a six-month randomised controlled trial assigned 77 women post-GDM to either a low-glycaemic index (LGI) diet or a conventional healthy dietary recommendation [48]. The study reported that women in the LGI diet group lost significantly more weight and improved 2 h postprandial glucose levels. A few limitations of the use of the 3-day food record were underreporting by the subjects and the inability to capture the subjects’ habitual dietary patterns [48]. Hence, we propose the combination of a traditional dietary assessment together with a metabolomics approach to produce a more objective dietary assessment method. Additionally, dietary patterns of Malaysians may be different from those of the Caucasian population [10] and warrant further investigation in relation to T2D risk in this population.

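### The continuous secondary outcomes are compared by a one-way ANOVA without covariates, although time since GDM is neither limited nor balanced and probably differs between the groups

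*Protocol article*

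**What the plan says.** Section 2.1 of the protocol article defines the comparisons: "The secondary outcomes of the study include the comparisons of anthropometric and clinical measurements, biochemical profile, energy and nutrient intake, and lifestyle practices", across the three glycaemic groups. Aim (e) repeats this. Section 2.7 names the tests. Continuous variables get "one-way analysis of variance (ANOVA) to compare the differences between the three groups". Categorical variables get "the Chi-squared test to determine the association between categorical variables". Neither carries a covariate.

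On who enters, Section 2.3 states "The study will include Malaysian women aged 18–49 years with a previous diagnosis of GDM". It excludes pregnant women and those with "previously diagnosed medical problems (such as type 1 or type 2 diabetes, cancer, and liver or renal disorders", but sets no minimum or maximum time since the GDM pregnancy. Section 2.4 plans systematic random sampling, with no matching or stratification on time.

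On time itself, Section 2.5.2 collects age and "duration lapse since GDM diagnosis". Section 2.7 plans a subgroup analysis at under 1 year versus 1 year or more, and reports that an earlier study found different T2D risk factors in the two periods. It also plans a multinomial logistic regression with crude and adjusted odds ratios, into which a variable enters as a confounder only if it is significant at the bivariate level. The Discussion gives a T2D prevalence that "ranges between 0.8% and 6 weeks to 35.5% at 15 years postpartum" (the first 'and' is read here as 'at').

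**The concern.** If T2D becomes more common as years pass, women classed as T2D will on average be further from their GDM pregnancy than women classed as NGT or prediabetes. They will also tend to be older, since age advances with elapsed time. Any outcome that changes with time since delivery or with age will then differ between the groups even if it has nothing to do with T2D. A one-way ANOVA cannot separate the two sources.

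At stake is the interpretation of aim (e): a difference in body composition, intake, lipids or sleep could be reported as a characteristic of T2D when it partly reflects how long ago the pregnancy was.

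**Working it through.** **Inputs from the article.** Prevalence 0.8% at 6 weeks (6/52 = 0.115 years) and 35.5% at 15 years (Discussion); minimum sample 126 and 20% non-response (Section 2.3); significance level 0.05 (Section 2.7).

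**Assumptions, none of them in the article.** The enrolment window and the distribution of time within it; a straight line between the two prevalence points; prediabetes constant at 25%; a correlation r between the outcome and time since GDM.

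**The plan's own figure.** If the 99 women are three equal groups of 33, then 33/0.8 = 41.25, rounded up to 42, and 3 × 42 = 126. This matches.

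**Step 1: gap in time since GDM.** The prevalence slope is s = (0.355 − 0.008)/(15 − 0.115) = 0.0233 per year. For enrolment uniform from 0.115 to b years, with mean prevalence P and time variance V = (b − 0.115)²/12, the difference in mean time between T2D and non-T2D women is sV / [P(1 − P)].

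- 15-year window: P = (0.008 + 0.355)/2 = 0.1815; V = 14.885²/12 = 18.46; gap = 0.0233 × 18.46 / (0.1815 × 0.8185) = **2.9 years** (9.9 v 7.0).
- 5-year window: prevalence at 5 years = 0.008 + 0.0233 × 4.885 = 0.122; P = 0.065; V = 4.885²/12 = 1.99; gap = 0.0233 × 1.99 / (0.065 × 0.935) = **0.76 years** (3.3 v 2.5).

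With a logistic instead of a linear prevalence curve, the gaps are 4.2 and 0.55 years. For a 2-year window they are only 0.08 to 0.24 years. If enrolment is skewed to early years (exponential, mean 3 years) but reaches 15 years, they are 2.5 to 3.4 years.

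**Step 2: what the ANOVA would show.** Studies of 126 women were simulated with linear prevalence and uniform enrolment. The outcome was r × (standardised time) plus independent noise, with no effect of group. Share of studies with p < 0.05 at r = 0.3:

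| Window | One-way ANOVA | ANCOVA on time |
|---|---|---|
| 5 years | about 6% | about 5% |
| 15 years | about 12% | about 5% |

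At r = 0.2 and a 15-year window the ANOVA figure is about 8%.

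**Step 3: equal groups.** If recruitment fills groups of 42, the T2D group is larger than its natural share (126 × 0.1815 = about 23 in the 15-year case). For the 15-year window the within-group SD of time is 4.05 years, so the spurious standardised difference at a within-group r of 0.3 is 0.3 × 2.90/4.05 = 0.21. The noncentrality is 42 × (2/3) × 0.215² = 1.29, and the ANOVA rejects in about 16% of studies. For the 5-year window the same calculation gives about 11%. With the logistic curve the figures are 31% and 8%.

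**Step 4: how far the bivariate rule helps.** In the Step 2 simulation, time since GDM itself differs significantly across the three groups in about 80% of studies with a 15-year window and about 23% with a 5-year window. The rule would therefore usually bring time into the multinomial model where the gap is large and often miss it where the gap is small. In neither case does it alter the group means compared by ANOVA.

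**The case against.** The strongest reply is that the article never says how far back recruitment reaches. One site includes a maternal and child health clinic, so recent deliveries may dominate, and with a short window the distortion is negligible. Known T2D is excluded, so the T2D group consists of newly detected cases. If the cited prevalences include known cases, the gradient among eligible women is flatter than used above. Both points stand, and they make the size uncertain. They do not remove the concern, because nothing in the plan secures a short window or a flat gradient.

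A second reply is that time is not ignored: there is an early/late subgroup and an adjusted multinomial model. This also stands in part. But the split at 1 year leaves every later year in one stratum, and the multinomial model yields odds ratios, not adjusted group means.

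A third reply is that covariates for secondary comparisons may be left to an analysis plan that is not shown. Here, however, the article names a specific unadjusted test for the named comparisons, so the point is about a stated choice.

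A reader might also infer three stronger claims that the article does not support:

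- That the comparison groups will certainly be years closer to the pregnancy. That needs enrolment reaching well beyond 5 years.
- That every secondary outcome goes only to an unadjusted ANOVA. Categorical outcomes go to Chi-squared, and the adjusted model exists alongside.
- That the type I error is inflated. The ANOVA tests equality of unadjusted means, and rejecting is correct when those means differ. The problem is confounded interpretation.

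**Conclusion.** The point holds in a limited form. The continuous secondary outcomes are compared without adjustment, the design does not limit or balance time since GDM, and the article's own prevalence figures make a longer interval and greater age in the T2D group likely. The direction is well supported; the size is not known. Under the linear, uniform assumptions the effect at r = 0.3 runs from hardly visible (5-year window, about 6% of studies) to moderate (15-year window, about 12%), and is somewhat larger if the groups are filled equally. No correlation between any outcome and time since GDM is given in the article, so r is purely illustrative. The article also states that the study is cross-sectional and limited to associations, which softens the consequence. The change is worth making because it is nearly free and uses variables already collected.

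**What to change.** In Section 2.7:

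- Keep the one-way ANOVA as the descriptive comparison.
- For each continuous secondary outcome, add a linear model (ANCOVA) of group with age and time since GDM as pre-specified covariates. Use the adjusted means and differences when interpreting group differences.
- Force the same two covariates into the multinomial model, whatever their bivariate significance.
- Add breastfeeding only if current status can be derived, since Section 2.5.2 lists its duration and not current status.

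The cost is two degrees of freedom per linear model among at least 126 women, a little more analysis and reporting, and no new data. The multinomial model gains two terms for each outcome contrast, which matters more if the T2D group turns out small.

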#### 2.5.1. Diagnosis of Type 2 Diabetes and Prediabetes

After an overnight fast of 8–12 h, subjects will undergo a 75 g, 2 h OGTT. Blood and urine samples will be taken for HbA1c, insulin, lipid profile, and metabolomic analysis. Subjects will be grouped into either NGT, prediabetes or T2D based on their OGTT and HbA1c results, as advised by the study endocrinologist. Our diagnostic criteria for T2D and prediabetes are based on the Malaysian Clinical Practice Guidelines [7] (Table 1).

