#### 2.5.3. Dietary Patterns

The study dietitian will administer a semiquantitative food frequency questionnaire (FFQ) adapted from the nationwide Malaysian Adult Nutrition Survey, to determine food consumption in the past month [21]. It contains 14 food groups: grain and cereal products; fast food; meat and poultry; fish and seafood; eggs; legumes, seeds and nuts; milk and dairy products; vegetables; fruits; beverages; alcoholic drinks; confectionaries; bread spread; and condiments. The portion size of the food items will be according to the Food Portion Sizes of Malaysian Foods Album [22]. The amount consumed food will then be converted into grams per day for each food item [10].

Dietary patterns will be derived based on PCA. Data suitability for factor analysis will be assessed prior to performing PCA [23,24]. Food items will be classified based on similarities in nutrient profiles and previous local studies [24,25,26]. The factor scores will be orthogonally rotated by varimax transformation to increase loading differences for easier interpretability [24,27]. Eigenvalue cut-off > 1.5 will determine the number of factors [28]. Food items with factor loadings < ±0.3 will be removed from further analysis [24,28]. A high factor score, whether positive or negative, indicates a high intake of that food group in dietary pattern; and vice versa [23,27].

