#### 2.5.7. Biochemical Profile

Subjects will be asked to fast overnight for 8–12 h prior to blood collection. Fasting venous blood samples will be drawn by a trained phlebotomist. Blood samples for conventional biochemical parameters (glucose, HbA1c, insulin, and lipid profile) will be transported to an established commercial laboratory for analysis (Clinipath Sdn. Bhd., Bangsar, Malaysia). Venous blood will be drawn at 2 h following the administration of a 75 g glucose solution drink to obtain the postprandial glucose level.

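### Choosing confounders by bivariate p-value lets variables that define the glycaemic groups into the adjusted models and often misses moderate true confounders

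*Protocol article*

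**What the plan says.** Section 2.7 plans the main association model: "Multinomial logistic regression will determine the factors, and the nutritype signature models associated with T2D". Crude and adjusted odds ratios are to be presented. The only rule for adjustment is "Variables significant at the bivariate level will be entered into the regression model as confounders", with "value < 0.05 for all statistical tests will be considered significant". For comparisons across groups the section names "one-way analysis of variance (ANOVA) to compare the differences between the three groups".

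Section 2.5.1 defines the outcome: "Subjects will be grouped into either NGT, prediabetes or T2D based on their OGTT and HbA1c results". Table 1 gives cut-offs for fasting glucose, 2-h glucose and HbA1c. Section 2.5.7 measures the "conventional biochemical parameters (glucose, HbA1c, insulin, and lipid profile"), and Section 2.1 lists the biochemical profile among the secondary comparisons between the same three groups.

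Section 2.5.2 collects time since the GDM diagnosis, pre-pregnancy weight and family history of diabetes. Section 2.7 otherwise uses time since GDM only for a subgroup split at one year.

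**The concern.** A p-value in the study sample does not show whether a variable is a confounder. The rule can go wrong in two directions.

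- **Wrong variables enter.** A measure that defines the outcome differs between the groups by construction. Under the rule as worded it becomes a covariate. Insulin and lipids may lie on the path from diet to diabetes or follow from diabetes, and would enter on the same footing.
- **Right variables drop out.** A real confounder of moderate strength can miss p < 0.05 in a sample of this size and is then left out.

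The adjusted odds ratios for dietary patterns and nutritype signatures depend on this rule, and they serve aims (a) and (d) in Section 2.1. Adjusting for glucose or HbA1c would ask whether diet is associated with diabetes among women with the same glycaemia, which is not the study question.

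**Working it through.** **1. The plan's own figures.** Section 2.3 gives 99 subjects, raised to 126 for 20% non-response. If the 99 are three groups of 33, then 33 / (1 − 0.20) = 41.25, rounded up to 42, and 3 × 42 = 126. The total therefore fits equal groups, although no group size is stated. The 99 cannot be recomputed because no mean difference or SD is given.

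**2. How many T2D cases there may be.** Women with known type 2 diabetes are excluded, sampling is systematic random, and no quota per group is stated. The Discussion cites a prevalence that "ranges between 0.8% and 6 weeks to 35.5% at 15 years postpartum", read here as 0.8% at 6 weeks to 35.5% at 15 years. Applied to 126 women: 0.008 × 126 = 1.0 and 0.355 × 126 = 44.7. Applied to 99: 0.8 and 35.1. The count could be anywhere from very small to about the size of an equal group.

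**3. Chance that the screen finds a true confounder.** Assume a continuous confounder with means 0, d/2 and d (in SD units) in NGT, prediabetes and T2D, tested by one-way ANOVA at 0.05. The noncentrality is λ = Σ nᵢ(μᵢ − μ̄)², and power is the probability that a noncentral F with 2 and N − 3 degrees of freedom exceeds the 5% critical value.

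- 42/42/42, d = 0.5: μ̄ = 0.25; λ = 42 × (0.0625 + 0 + 0.0625) = 5.25; power 0.51.
- 33/33/33, d = 0.5: λ = 33 × 0.125 = 4.125; power 0.42.
- 59/30/10 (assumed split of 99), d = 0.5: μ̄ = (30 × 0.25 + 10 × 0.5) / 99 = 0.126; λ = 0.94 + 0.46 + 1.40 = 2.80; power 0.29.

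| Groups (NGT/prediabetes/T2D) | d = 0.3 | d = 0.5 | d = 0.8 |
|---|---|---|---|
| 42/42/42 | 0.21 | 0.51 | 0.91 |
| 33/33/33 | 0.17 | 0.42 | 0.83 |
| 59/30/10 | 0.13 | 0.29 | 0.65 |

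At d = 0.5 the screen misses the confounder 1 − 0.51 = 49% of the time in the most favourable of these layouts and 1 − 0.29 = 71% in the least favourable.

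**4. What a miss costs.** In a simulation with N = 99, 2,000 runs per scenario, one confounder and an exposure with no effect, the median odds ratio was about 1.00 with full adjustment and 1.03 to 1.07 after screening. Type I error stayed near nominal.

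**5. What happens to the defining measures.** In simulated samples, fasting glucose, 2-h glucose and HbA1c each passed the screen at least 99.5% of the time. With T2D assigned when any one cut-off is met, complete separation of T2D from the rest occurred in at most 1.5% of samples for a single measure. With all three entered it rose from 0.5% to 30% as the assumed correlation between them rose from 0.4 to 0.8. The exact rates depend on the assumed distributions. A single variable that alone defined the groups separated them in 50 of 50 fits, but that is not how this article defines T2D.

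**The case against.** The best defence is that the article never says glucose or HbA1c will be covariates. It lists the biochemical profile as an outcome, uses glucose and HbA1c for diagnosis, and speaks of confounders, which an outcome-defining variable is not. A sensible analyst would leave these variables out. That is fair, but the analyst would have to depart from the written rule to do so, and it gives even less guidance on insulin and lipids. An article may leave a covariate list to a fuller plan; here it fixes a rule instead, and the rule is poor.

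Several stronger readings are tempting and are not supported:

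- *Perfect separation is certain.* It is not. Three cut-offs are in play, and a woman may meet one with ordinary values on the others.
- *The T2D group will be small.* No group size is stated, and 126 fits 42 per group. Small counts are possible, not established.
- *Time since GDM will be lost.* It may well pass. If the two cited prevalences are the ends of a logistic curve and women are spread evenly from 6 weeks to 15 years, the screen selects it about 94% of the time; over 0 to 10 years, about 35%. Both are assumed spreads.
- *The nutritype signatures are compromised.* Section 2.5.9 derives them by PLS-DA, which this rule does not touch. Only the later regression is affected.

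The article also limits itself to associations at a single time point, which lowers the stakes but does not make an over-adjusted odds ratio interpretable. Whether pattern scores built from absolute intake ("The amount consumed food will then be converted into grams per day for each food item") should be energy-adjusted is a separate question.

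**Conclusion.** The point holds as a rule that is fixed badly, and it should be corrected, though it does not undermine the study as a whole. Two conclusions stand. First, followed as worded, the rule admits group-defining measures almost surely and possible mediators or consequences whenever they reach p < 0.05; the result is over-adjustment and possible instability. Second, the screen is unreliable for moderate confounders even with equal groups of 42 (power 0.51 at d = 0.5), and more so with few T2D cases (0.29 with 10 of 99).

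The first is the more serious, since the simulated bias from omitting one confounder was small (odds ratio 1.03 to 1.07 where the truth is 1). The effect sizes, the linear trend across groups, the 10-case scenario and the any-cut-off reading of Table 1 are assumptions; the documents give no figures that would replace them.

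**What to change.** Replace the sentence in Section 2.7 with the following elements:

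- A small covariate set named in advance on subject-matter grounds from variables already collected, for example age, time since GDM, and pre-pregnancy BMI or family history of diabetes. Its size should be capped by the number of T2D cases observed, with an order of priority so that the cap does not reopen the choice.
- Total energy intake, from the dietary recalls, added where dietary pattern scores are the exposure, if the case count allows.
- A statement that glucose, HbA1c and insulin are never covariates in models of glycaemic group.
- Penalised estimation as a sensitivity analysis if the T2D group proves small.

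The set should be fixed before the group comparisons are seen, since a later choice would look data-driven. No new data are needed. The cost is a change of wording and a few degrees of freedom spent on covariates that may prove unimportant.
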